### Outcomes {12}

#### Primary outcome

The primary outcome measure is the comparison of the 48-h postoperative oxygenation index between the two cohorts. This will be derived from arterial blood gas sampling and analysis, in addition to the FiO_2_ 48th h postoperatively.

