### Sample size {14}

This randomized controlled trial aimed to examine the effect of varying intraoperative oxygen concentrations on PPCs. This study is a superiority trial in which the optimal effect threshold has been set. Based on a preliminary experiment, 10 samples were collected each group, and the values of oxygenation index were expressed as mean ± standard deviation: 384 ± 85 mmHg for 40% group and 340 ± 60 mmHg for 80% group. This study was designed as a superiority trial, with a clinically significant difference defined as an increase in oxygenation index by at least 30 (10% of 300 acute lung injure oxygenation index) in favor of 40% group compared to 80% group. The pooled standard deviation was estimated to be 74 mmHg. The sample size required for each group to achieve a significant difference, with a one-sided *α* = 0.025 and *β* = 0.20. The minimum sample size required for each group was approximately 439, with a total of 1098 samples needed for both groups, considering a dropout rate of 20%.

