### Recruitment {15}

Participants will be enrolled through being scheduled for surgical procedures, such as laparoscopic gastrointestinal surgery for cancer. For prospective recruitment, an information sheet will be provided regarding the trial objectives, workflow, and randomization procedures. Prior to the procedure, the participant will provide written informed consent. In cases where the participant is unable to do so, a legally authorized representative or caregiver will be contacted to provide consent on behalf of the participant, in accordance with the GCP guidelines.

Preoperative visits will be conducted; and the inclusion and exclusion criteria will be strictly employed. Participants who meet all the eligibility criteria and provide written informed consent will be eligible for enrollment. A trained research team will recruit participants and use standard randomization procedures, to assign them to the study population on the preoperative day. The anesthesiologist will only be notified of this assignment the day after the participant is admitted to the ward.

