## Statistical methods

### Statistical methods for primary and secondary outcomes {20a}

The oxygenation index data for the two cohorts will be collected, based on a preliminary experiment. The oxygenation index values will be presented as means and standard deviations.

The Student’s *t*-test will be used to assess the disparities between the two cohorts for continuous outcome variables adhering to a normal distribution. In cases of non-normal distribution, the Mann–Whitney test will be used. Categorical data will be analyzed, using the chi-squared or Fisher’s exact tests. These tests are one-sided, and statistical significance will be set at *p* < 0.025. The parameters will be computed and displayed, including approximations and a 97.5% confidence interval.

The primary and secondary outcome indicators will be evaluated using linear and generalized linear mixed-effects models.

A linear mixed-effects model was employed to analyze the primary outcome measures (oxygenation index and quantitative variables). The model included patient baseline data (age, gender, BMI, and prior SARS-CoV-2 infection history), intraoperative characteristics (anesthesia duration, intraoperative crystalloid volume, intraoperative colloid volume, surgical duration, surgical position, pneumoperitoneum pressure, intraoperative PEEP, occurrence of pulmonary re-expansion, intraoperative ventilator tidal volume, and airway platform pressure), and center and group factors.

For quantitative secondary outcome measures—including postoperative PACU oxygen duration, 24-h and 48-h oxygen therapy duration, and postoperative blood gas parameters (pH, partial pressure of carbon dioxide, and lactate) at 48 h—linear mixed-effects models were employed. The model included patient baseline characteristics (age, gender, BMI, and prior SARS-CoV-2 infection history) and intraoperative parameters (anesthesia duration, intraoperative crystalloid volume, colloid volume, surgical duration, surgical position, pneumoperitoneum pressure, intraoperative PEEP, occurrence of pulmonary re-expansion, and ventilator tidal volume), along with center and group factors.

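### The primary oxygenation-index model omits preoperative oxygen saturation, a baseline value that eligibility requires for everyone: a modest missed gain in precision, not a bias

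*Protocol article*

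**What the plan says.** The Primary outcome section states: "The primary outcome measure is the comparison of the 48-h postoperative oxygenation index between the two cohorts". The Statistical methods section {20a} gives the model: "A linear mixed-effects model was employed to analyze the primary outcome measures (oxygenation index and quantitative variables". It then lists the terms: "The model included patient baseline data (age, gender, BMI, and prior SARS-CoV-2 infection history", ten intraoperative variables (from anesthesia duration to airway plateau pressure), center and group. No term in the list describes oxygenation before surgery. The secondary-outcome models in the same section also contain none.

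Eligibility criteria {10} sets a floor of 94% on preoperative oxygen saturation as an inclusion criterion and repeats the limit as an exclusion. Recruitment {15} applies the criteria to everyone at a preoperative visit: "Participants who meet all the eligibility criteria and provide written informed consent will be eligible for enrollment". Sequence generation {16a} places randomisation on the day before surgery. The visible text mentions blood gases only as postoperative measurements.

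**The concern.** The endpoint is a single postoperative measurement of how well the lungs oxygenate. Some of its spread between participants may reflect the oxygenation they brought to surgery, and a baseline measure of the same property is a natural covariate for removing that part. Eligibility cannot be judged without such a measure, so one should exist for every participant before allocation. The covariate list is explicit and long, yet it leaves this value out.

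What is at stake is the width of the confidence interval for the FiO2 effect, and the extent to which a chance difference in baseline oxygenation between the groups stays in the estimate.

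**Working it through.** **Inputs from the Sample size section {14}**
- Pilot means and SDs, 10 per group: "384 ± 85 mmHg for 40% group and 340 ± 60 mmHg for 80% group", a difference of 384 − 340 = 44 mmHg.
- Superiority threshold: "an increase in oxygenation index by at least 30".
- SD: "The pooled standard deviation was estimated to be 74 mmHg". Check: √((85² + 60²)/2) = 73.6, which rounds to 74.
- Error rates: "one-sided *α* = 0.025 and *β* = 0.20".
- Dropout: 20%.

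**Step 1: reproduce the plan's own figure**

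n per group = 2 × SD² × (1.960 + 0.842)² / d².
- d = 44 − 30 = 14 gives 439 per group. Then 439/0.8 = 548.75, rounded up to 549, and 2 × 549 = 1098. Both stated figures are reproduced.
- d = 30 gives 96 per group, and d = 44 gives 45 per group. Neither matches.

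Of these readings, only superiority over a 30 mmHg margin, with an expected excess of 14 mmHg, gives the stated size. The calculation uses the raw SD and takes no credit for covariates.

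**Step 2: effect of adding the covariate**

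Let r be the partial correlation of preoperative saturation with the 48-h index, given the terms already in the model. Adding saturation multiplies the model's residual variance by (1 − r²). The documents give no value for r, so it is assumed over a range.

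To express this as power, the residual SD before the addition must also be assumed. It is taken here as 74 mmHg. That is the raw pilot SD, so it stands in for the residual SD of the adjusted model. Then:
- SD(r) = 74 × √(1 − r²)
- SE = SD(r) × √(2/439)
- power = Φ(14/SE − 1.960)

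| r (assumed) | Variance cut | SD, mmHg | SE, mmHg | Power at 439 per group | n per group for 80% power |
|---|---|---|---|---|---|
| 0 | 0% | 74.0 | 4.99 | 80.0% | 439 |
| 0.1 | 1% | 73.6 | 4.97 | 80.4% | 435 |
| 0.2 | 4% | 72.5 | 4.89 | 81.6% | 422 |
| 0.3 | 9% | 70.6 | 4.76 | 83.6% | 400 |

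The half-width of the interval (1.96 × SE) goes from 9.79 mmHg at r = 0 to 9.74, 9.59 and 9.34 mmHg.

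**Step 3: which part of the table is firm**

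The variance-cut column follows from r alone. The SD, SE, power and n columns also depend on the 74 mmHg stand-in. If the listed covariates and center already explain part of the variance, the starting SD is lower and starting power higher, and the gain in power points differs.

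**The case against.** The strongest reply is that nothing here is wrong. Randomisation makes the comparison unbiased with or without this covariate, and the test's error rate already allows for chance imbalance. The sample size never counted on covariates, so 1098 stands. All of that is correct. A reader might infer that the omission biases the FiO2 comparison or leaves the trial undersized; the documents support neither.

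The gain may also be slight. Eligible saturations lie between 94% and 100%, and so narrow a range tends to weaken a correlation. At r of 0.2 or less the gain is under 2 power points. This stands, and it limits the point to a modest one. A reader might be tempted to assume a stronger correlation and claim the equivalent of many extra participants; nothing in the documents supports that.

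Three objections bear on the remedy:
- **The value itself.** The eligibility section sets a threshold. It does not say that the continuous reading is entered on the case report form, or under what inspired oxygen it is taken. The monitoring on arrival described under Intervention description {11a} is no safe substitute, since allocation is on the preoperative day and the arrival reading may come after it.
- **Figure 2.** The assessment schedule is not shown and could list a preoperative blood gas. Saturation would then not be the best baseline measure. Such a gas would still be missing from the model's named terms, so the omission remains and only the choice of covariate changes.
- **The test.** The same section also names a t-test or Mann–Whitney test for continuous outcomes and does not clearly rank these against the mixed model. A covariate helps only the mixed model.

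These objections shape the fix. None is a reason to leave a baseline measure out.

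**Conclusion.** The point holds as a missed gain in precision. The primary model names its covariates and omits the only baseline oxygenation measure in the visible text, one that eligibility requires for every participant.

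The likely size is small: a 1%, 4% or 9% cut in residual variance for assumed partial correlations of 0.1, 0.2 or 0.3. Taking 74 mmHg as the residual SD and 439 analysed per group, power would be about 80.4%, 81.6% or 83.6%, against 80.0% without the covariate. The correlation is not documented, and the entry floor makes the lower values more plausible.

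The recommendation rests on the near absence of cost, not on a large expected benefit.

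**What to change.** Before unblinded data are examined, add preoperative oxygen saturation to the primary mixed model in section {20a} as a continuous fixed covariate. Use the value from the eligibility assessment, not the arrival reading. If a preoperative blood gas or oxygenation index is collected, use that in its place. First confirm that the numerical value, and not only a tick against the 94% limit, is recorded for all participants.

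The statistical cost is one degree of freedom out of about 878 analysed participants (2 × 439). A value required for entry should add little missing data. The administrative cost is a documented amendment. With three interim analyses planned and an estimated end date of 31 December 2025, the amendment should record whether any outcome data by group had been seen when the change was made. If they had, report the adjusted model with this covariate as a sensitivity analysis.

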## Introduction

### Background and rationale {6a}

The World Health Organization (WHO) and United States Center for Disease Control recommend the use of 80% oxygen in the perioperative period, to reduce surgical site infections after general anesthesia [1, 2]. Moreover, clinical anesthesiologists use pure oxygen during the induction and awakening phases of general anesthesia to prevent hypoxemia, particularly in patients with a risk of difficult airways and critical illnesses [3, 4].

However, controversy exists regarding the safety of the perioperative use of a high fraction of inspired oxygen (FiO_2_). With a difficult airway, 100% FiO_2_ is usually administered during a short period, due to the risk of prolonged apnea. In particular, this short inhalation of pure oxygen causes absorption atelectasis in 90% of patients [5, 6], which may be present postoperatively [7, 8]. Absorption atelectasis results in reduced lung compliance, oxygen damage, and impaired oxygen delivery and lung function. The results of a meta-analysis have revealed an association between decreased oxygen levels and parameters and increased atelectasis severity, after high FiO_2_ during anesthesia [9, 10].

Postoperative atelectasis is an important risk factor for postoperative pulmonary complications (PPCs), such as pneumonia, resulting in increased postoperative morbidity and mortality rates and prolonged hospital stays [11–13]. Therefore, PPCs are severe and are of particular concern in older adult patients undergoing laparoscopic gastrointestinal surgery.

A study involving 73,992 participants found that a high FiO_2_ increases PPCs and the 30-day postoperative mortality rate [14].

Moreover, further studies have uncovered that in acute and severe cases, the administration of high concentrations of FiO_2_ does not improve important clinical outcomes and results in an increased mortality rate [15].

Conversely, the findings of a few meta-analyses have revealed that the use of high FiO_2_ during general anesthesia does not increase postoperative mortality, intensive care unit (ICU) occupancy, pneumonia, and atelectasis [16, 17]. Furthermore, the results of a controlled intervention trial comprising 5749 patients have revealed the absence of an effect of high FiO_2_ levels on 30-day mortality rates or wound healing [18, 19].

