### Criteria for discontinuing or modifying allocated interventions {11b}

The FiO_2_ will be adjusted to 40% and 80% in the L and H cohorts, respectively. Should the intraoperative oxygen saturation of the participants in the L cohort decline to < 94%, while the PEEP remains at 30 cm H_2_O, at a duration of ≥ 30 s, without an improvement in the oxygen saturation, the oxygen concentration will be increased to 80%.

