## Assignment of interventions: allocation

### Sequence generation {16a}

Post-initiation of the study, each clinical trial site will continuously screen eligible participants and enroll them in the trial. Participants will be randomly assigned. The study employed block randomization with center stratification, where each center competed for inclusion. The electronic data capture (EDC) system generated the randomization. The participants will be assigned to two cohorts, as per a 1:1 ratio, on the preoperative day. To balance the variables, we will stratify the participants according to the following factors: age, surgical position, area of the clinical trial site, operative time, and the anesthetic drug administration and method.

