For qualitative data of secondary outcomes—including postoperative PACU oxygenation rate, 24-h postoperative oxygenation rate, 48-h postoperative oxygenation rate, pulmonary complications at 7 days postoperatively, and 30-day mortality rate—generalized linear mixed-effects models were employed. The model included patient baseline data (age, gender, BMI, and history of SARS-CoV-2 infection), intraoperative characteristics (anesthesia duration, intraoperative crystalloid volume, intraoperative colloid volume, surgical duration, surgical position, pneumoperitoneum pressure, intraoperative PEEP, occurrence of pulmonary re-expansion, intraoperative ventilator tidal volume, and airway platform pressure), and center and group factors.

For ordinal outcomes such as postoperative PACU oxygen concentration, 24-h postoperative oxygen concentration, 48-h postoperative oxygen concentration, and severity of pulmonary complications, a generalized linear mixed-effects model was employed. The model included patient baseline data (age, gender, BMI, history of SARS-CoV-2 infection), intraoperative characteristics (anesthesia duration, intraoperative crystalloid volume, intraoperative colloid volume, surgical duration, surgical position, pneumoperitoneum pressure, intraoperative PEEP, occurrence of pulmonary re-expansion, intraoperative ventilator tidal volume, and airway platform pressure), and center and group factors.

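### The mixed models adjust the group effect for variables arising after randomisation, some plausibly on the path from FiO2 to lung function, so the adjusted coefficient need not be the intention-to-treat effect

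*Protocol article*

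**What the plan says.** All references are to the protocol article.

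- **Timing.** Sequence generation {16a}: "The participants will be assigned to two cohorts, as per a 1:1 ratio, on the preoperative day".
- **Primary model.** Section {20a} specifies a linear mixed model with group, centre, four baseline items (age, sex, BMI, previous SARS-CoV-2 infection) and ten intraoperative items. The intraoperative list opens with "intraoperative characteristics (anesthesia duration, intraoperative crystalloid volume, intraoperative colloid volume" and continues with "surgical duration, surgical position, pneumoperitoneum pressure, intraoperative PEEP, occurrence of pulmonary re-expansion, intraoperative ventilator tidal volume, and airway platform pressure".
- **Binary and ordinal secondary models**, which cover 7-day pulmonary complications and 30-day mortality, use the same list, ending "occurrence of pulmonary re-expansion, intraoperative ventilator tidal volume, and airway platform pressure), and center and group factors".
- **Quantitative secondary models** leave out airway platform pressure but keep the other nine items: "pneumoperitoneum pressure, intraoperative PEEP, occurrence of pulmonary re-expansion, and ventilator tidal volume), along with center and group factors".
- **Unadjusted tests.** Section {20a} also plans a t-test or Mann–Whitney test for continuous outcomes and a chi-squared or Fisher test for categorical ones, one-sided at 0.025. It does not rank these against the models.
- **Principle.** Section {20c} says that primary, secondary and safety outcomes follow intention to treat.
- **Mechanism.** Background and rationale {6a}: "Absorption atelectasis results in reduced lung compliance, oxygen damage, and impaired oxygen delivery and lung function".
- **Arm-specific rule.** Section {11b} describes a step for desaturation in the L cohort which involves airway pressure and, "without an improvement in the oxygen saturation, the oxygen concentration will be increased to 80" (per cent). No matching rule is given for the H cohort.

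**The concern.** Randomisation makes the arms comparable at the time of assignment. A covariate measured later can itself be changed by the assigned oxygen fraction. Adjusting for it can then do two things. It can remove the part of the effect that passes through the covariate. It can also open a path through unmeasured causes, such as the underlying state of the lung, that affect both the covariate and the outcome.

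The protocol supplies the reason to expect this for at least two variables. If high oxygen causes atelectasis and lowers compliance, then at a given tidal volume and PEEP the airway platform pressure rises, and re-expansion may be needed more often. Both would be steps on the path from FiO2 to the oxygenation index. Recorded PEEP could differ by arm through the L-cohort rule in {11b}, and fluid volumes could differ because the anaesthetist knows the allocation ({17a}).

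At stake is the meaning of the group coefficient for the primary outcome and for the modelled secondary outcomes. The design leaves little room: the assumed difference exceeds the superiority margin by only 14 mmHg.

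**Working it through.** **1. Reproduce the plan's sample size ({14}).** Inputs: pilot means 384 and 340 mmHg (difference 44), margin 30, SD 74, one-sided alpha 0.025, power 80%, dropout 20%.

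- Pooled SD: √((85² + 60²)/2) = 73.6, stated as 74.
- n per group = 2 × 74² × (1.960 + 0.842)² / (44 − 30)² = 439 after rounding up.
- With dropout: 439/0.8 = 548.75, so 549 per group and 1098 in total.

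The stated figures reproduce, and only as superiority over a 30 mmHg margin with a true difference of 44. Without the margin, a difference of 30 needs 96 per group and a difference of 44 needs 45.

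**2. What adjustment does to the coefficient.** Take one standardised covariate M that the 40% arm shifts by a SD, that changes the outcome by b mmHg per SD, and that shares an unmeasured cause U with the outcome (correlation d with M, g mmHg per SD of U). Then

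adjusted coefficient = total effect − a × (b + g × d).

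The document gives none of a, b, g or d; all values here are assumed. The simulation used 439 per arm, 2000 runs and a within-arm SD of 74.

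| a | b | g | d | True total | Formula | Simulated |
|---|---|---|---|---|---|---|
| −0.3 | −25 | 0 | 0 | 44 | 44 − 7.5 = 36.5 | 36.5 |
| −0.5 | −25 | 0 | 0 | 44 | 44 − 12.5 = 31.5 | 31.4 |
| −0.3 | −25 | −25 | 0.5 | 44 | 44 − 11.25 = 32.75 | 32.9 |
| −0.3 | 0 | −25 | 0.5 | 44 | 44 − 3.75 = 40.25 | 40.3 |
| −0.3 | 0 | −25 | 0.5 | 0 | 0 − 3.75 = −3.75 | −3.9 |
| 0 | −25 | −25 | 0.5 | 44 | 44 | 44.0 |

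The unadjusted difference stayed within 0.15 mmHg of the true total in every row. Rows 4 and 5 show that the covariate need not be a mediator: being moved by the arm and sharing a cause with the outcome is enough. The last row shows no bias when FiO2 does not move the covariate. Reversing the sign of a in row 3 gives 44 + 11.25 = 55.25, so the direction is open as well.

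**3. What a loss of effect would cost.** SE = 74 × √(2/439) = 4.995. Power against the margin = Φ((effect − 30)/4.995 − 1.960).

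| Assumed share absorbed | Coefficient (mmHg) | Power against 30 mmHg |
|---|---|---|
| 0% | 44.0 | 80% |
| 10% | 39.6 | 48% |
| 20% | 35.2 | 18% |
| 30% | 30.8 | 4% |

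Against a null of zero, 39.6 and 35.2 mmHg lie 39.6/4.995 = 7.9 and 35.2/4.995 = 7.0 standard errors away, so power stays near 100%. The loss matters only for a test against the margin.

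**The case against.** - **The unadjusted tests are clean.** True. They are in {20a}, at the alpha used for the sample size, and the 439 per group reproduces as an unadjusted comparison of two means. A reader might infer that the protection of randomisation is lost for the primary outcome, complications and mortality; the document does not support that. But {20a} also says that the outcomes will be evaluated with the mixed models and never says which result decides, so the affected models may carry the conclusion.
- **Bias is not certain.** This stands. If FiO2 moves none of the covariates, the coefficient is unaffected. It would be too strong to say that the estimate is biased.
- **The variables are not equally suspect.** This stands too. Surgical position, pneumoperitoneum pressure and surgical duration are mainly surgical. Section {11a} gives both cohorts the same PEEP and tidal-volume ranges and the same regular recruitment. The case rests mainly on platform pressure and re-expansion, then on PEEP and fluids. The quantitative secondary models do not contain platform pressure at all.
- **The {11b} rule may rarely apply.** No frequency is given, so a material difference between arms in PEEP or re-expansion through this route is only possible. Separately, the PEEP figure in {11b} and the range in {11a} differ, and the authors should reconcile them.
- **The power figures are conditional.** They need the margin to be tested on the adjusted coefficient, which {20a} does not state, and a standard error that adjustment leaves unchanged. Prognostic covariates would normally reduce it.

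Two further inferences are not supported. One is that the mortality model would be unstable with so many covariates: no event rate is given. The other is that leaving out ASA class and preoperative saturation is an error: omitting a prognostic covariate from a randomised comparison does not bias it.

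**Conclusion.** The concern holds in limited form. Every {20a} mixed model conditions on variables that arise after randomisation. Pulmonary re-expansion (all models) and airway platform pressure (primary, binary and ordinal models) lie plausibly on the causal path that the protocol itself describes. The adjusted group coefficient can therefore differ from the total effect of assigned FiO2 that {20c} asks for. Neither the size nor the direction follows from the document.

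The fall from 80% power to about 48% or 18% is an illustration. It rests on an assumed 10% or 20% absorption, a margin test on the adjusted coefficient and an unchanged standard error. The unadjusted tests do not share the problem, so how far it reaches the trial's conclusion depends on a choice that the text leaves open.

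**What to change.** 1. In every confirmatory model in {20a}, keep only group, centre and covariates fixed before randomisation: age, sex, BMI, previous SARS-CoV-2 infection, and the stratification factors of {16a} in the form known preoperatively (for example, planned rather than actual surgical position).
2. Report the intraoperative variables descriptively by arm, or in models labelled exploratory.
3. State whether this baseline-adjusted model or the unadjusted test is the primary analysis, and whether the 30 mmHg margin is tested on it.
4. Optionally add preoperative oxygen saturation and ASA class, both already assessed for eligibility ({10}), to recover some precision.

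The cost is a change of wording and code. No new data are needed, and the sample size stays at 439 per group and 1098 in total. The downside is losing whatever reduction in residual variance the intraoperative variables would have given.

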**Methods:**

This multicenter, prospective, parallel-cohort, randomized controlled clinical trial will include 1098 older adult participants aged ≥ 65 years old undergoing laparoscopic gastrointestinal surgery, from 16 clinical trial sites across China. Participants will be randomized, as per a 1:1 ratio to two cohorts, the “L” and “H” cohorts, to receive low FiO_2_ (40%) and high FiO_2_ (80%) levels, respectively. The primary outcome measure is the 48-h postoperative oxygenation index between the two cohorts. The secondary outcome measures include the other blood gas analysis results, PPCs within 7 days, and 30-day mortality rate.

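### 30-day mortality is assigned a mixed model with 14 covariates plus centre and group, which is over-parameterised for the likely number of deaths and may have no finite estimate if mortality is about 1% or below

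*Protocol article*

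**What the plan says.** In the Protocol article, Statistical methods for primary and secondary outcomes {20a}, the qualitative secondary outcomes include "pulmonary complications at 7 days postoperatively, and 30-day mortality rate". One method is given for all of them: "30-day mortality rate—generalized linear mixed-effects models were employed". The covariates are listed in full:

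- four baseline terms: "patient baseline data (age, gender, BMI, and history of SARS-CoV-2 infection";
- ten intraoperative terms, beginning "anesthesia duration, intraoperative crystalloid volume, intraoperative colloid volume, surgical duration, surgical position, pneumoperitoneum pressure", then PEEP, and ending "occurrence of pulmonary re-expansion, intraoperative ventilator tidal volume, and airway platform pressure), and center and group factors".

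The list is not shortened for a rare outcome. The link function is not named; logistic is the usual reading. The text does not say whether centre is a random or a fixed term. The abstract has participants coming "from 16 clinical trial sites across China".

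Earlier in {20a} a second method appears: "Categorical data will be analyzed, using the chi-squared or" Fisher's exact tests, one-sided at 0.025. The section then says that primary and secondary outcomes will be evaluated with mixed models. It does not say which of the two governs mortality. No section gives an expected death rate or number of deaths.

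**The concern.** A model of this size needs many events. Eligibility criteria {10} suggest that deaths may be few: ASA I-III only, extubation planned in the operating room, and rejection of conversions to open surgery, bleeding above 800 ml, surgery over 8 h and life-threatening intraoperative events.

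With few deaths, the covariates can separate survivors from deaths perfectly, and maximum likelihood then has no finite solution. Even a finite fit rests on very little information per coefficient. The analyst would then have to drop terms or switch to the other named test after seeing the data. Mortality is a stated secondary objective, and the background section cites conflicting evidence on mortality under high oxygen, so readers will look for this result.

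**Working it through.** **Number of participants.** The Sample size section {14} gives a pilot difference of 384 − 340 = 44 mmHg, a margin of 30, an SD of 74, one-sided α = 0.025 and power 80%.

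n per arm = 2 × (1.960 + 0.842)² × 74² / (44 − 30)² = 438.6, so 439. With 20% dropout, 439 / 0.80 = 548.75, so 549 per arm and 1098 in total. The plan's figures reproduce exactly. If 20% are lost, 2 × 439 = 878 remain.

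**Number of slopes.** 4 baseline + 10 intraoperative + 1 group = 15 with centre random, counting surgical position as one term. With centre fixed, 16 − 1 = 15 more are added, giving 30.

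**Deaths per slope.** Expected deaths = 1098 × assumed rate. The rates are assumptions, because the documents give none.

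| Assumed 30-day mortality | Deaths | Per slope, 15 slopes | Per slope, 30 slopes |
|---|---|---|---|
| 0.5% | 5.5 | 0.37 | 0.18 |
| 1% | 11.0 | 0.73 | 0.37 |
| 2% | 22.0 | 1.46 | 0.73 |
| 3% | 32.9 | 2.20 | 1.10 |

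One death per slope needs 15 / 1098 = 1.37% mortality (15 / 878 = 1.71% after dropout). With fixed centres it needs 30 / 1098 = 2.73%.

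**Chance that an arm has no deaths.** This alone makes the group odds ratio infinite or zero. With equal mortality p in both arms, the probability is 2(1 − p)^549 − (1 − p)^1098. At 0.5%: 2 × 0.0638 − 0.0041 = 12%. At 1%: 0.8%.

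**Simulated separation, no centre term, n = 1098.** Several logistic simulations were run with 14 covariates plus group and no treatment effect. Deaths were unrelated to the covariates in one run, and two covariates were prognostic in others. Ranges cover the runs.

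| Assumed mortality | No finite fit | Group effect infinite |
|---|---|---|
| 0.5% | 33-41% | 15-21% |
| 1% | 5-9% | 1-3% |
| 2-3% | about 0% | 0% |

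The group column at 0.5% lies above the 12% from empty arms alone, as it should. At n = 878, no finite fit occurred in 47-52% of trials at 0.5% and 10-13% at 1%.

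**Fixed centres.** Some coefficient is infinite in 87-100% of trials over 0.5-3%. The group coefficient was not estimable in 37% at 0.5%, 1.5% at 1% and 0% from 1.5% upward.

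**Fewer covariates.** With only the four baseline covariates and no centre term, the fit still fails in 28% of trials at 0.5% and 3% at 1%.

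**The case against.** The strongest reply has four parts.

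- **The death rate is assumed, and a low one is not assured.** Participants are 65 or older, ASA III is allowed, and cancer surgery is included. Section {20c} analyses participants as randomized, so deaths among converted or heavily bleeding patients may stay in. This stands. A reader might infer that the model fails whatever the death rate, but at 2-3% a finite fit is nearly always found.
- **The fixed-centre failure rate does not measure damage to the treatment effect.** A reader might take 87-100% to mean that the treatment odds ratio is almost always unusable. Most of it comes from centres without deaths, whose own terms diverge while the group effect can stay finite. In a mixed model, centre is also more naturally a random term. This stands.
- **Rarity drives non-existence more than the covariate list does.** Going from 14 to 4 covariates only lowers failure from 33% to 28% at 0.5% in the same simulation. This also stands, and it means that pruning the list is not a sufficient cure.
- **Fisher's exact test is already named, and a fallback for non-convergence belongs in an analysis plan.** This stands in part. A reader might infer that mortality is left without any usable comparison, which is wrong. But the article specifies the mixed model in full for mortality and names a competing test without ranking them. That is a choice made in this document, not a detail left open for another.

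**Conclusion.** The point holds as one about a badly suited model and an unranked pair of analyses. Below about 1.4% mortality the model has fewer than one death per slope even with centre random. Failure to obtain a finite fit is a material risk near 0.5% and a smaller one at 1%. At 2-3% the model can usually be fitted, but 1.5-2.2 deaths per slope is still far too few for 15 slopes.

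This rests on an assumed mortality range of 0.5-3%, a logistic link, surgical position as a single term, and simulations without a centre term standing in for a random-centre fit.

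A reader might also regard mortality as the trial's key safety outcome. The documents do not call it that; it is listed last among the secondary outcomes. The point is minor to moderate and touches neither the primary analysis nor the sample size.

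**What to change.** Take 30-day mortality out of the mixed-model list in {20a} and state its analysis separately, for example:

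*Deaths within 30 days will be reported by group with the number of participants assessed. The governing analysis is Fisher's exact test, with a risk difference and an exact confidence interval at the trial's stated error level. If an adjusted estimate is reported, it will come from Firth-penalised logistic regression with group and age only, and will be supportive.*

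The cost is wording only, with no change to sample size or conduct. The downside is that the main mortality estimate is not adjusted for covariates or centre. The exact test adds no information when deaths are few. Its gain is a result that always exists and a choice of method made before the data are seen.
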